#### Analysis

The primary outcome is the change of BMI during the 12th week after minimization. To determine differences between the 2 groups after 12 weeks, analysis of covariance (ANCOVA) will be used to adjust for baseline values. Because there are two primary analyses (electro-acupuncture plus lifestyle modification versus lifestyle modification alone), Bonferroni correction will be used to address multiple testing, and a significance level of 0.05 will be used.

Statistical analyses of primary and secondary outcomes will be conducted as follows. First, all the analyses will be based on the intention-to-treat (ITT) principle. All patients, who will provide baseline data, will be included in the analyses, regardless of whether or not they complete the treatment or adhere to the protocol. Data distribution is expected to be normal, and skewed distribution data will be transformed prior to analysis. The statistical hypotheses are:

H_0_: acupuncture plus lifestyle modification = lifestyle modification (null hypothesis) versus H_1_: acupuncture plus lifestyle modification ≠ lifestyle modification (alternative hypothesis).

ANCOVA will be subsequently performed on BMI, body weight, and waist-to-hip ratio data as well as SF-36 and IWQOL-Lite. SF-36 and IWQOL-Lite will be transformed to continuous variables before analysis. Missing values will be addressed using the methods of last observation carried forward (LOCF). To address the results of objective outcomes, logistic regression analysis will be used to analyze dependent variables, including TC, HDL, and TG levels. These statistical analyses will be performed using SPSS 15.0 statistics software (SPSS Inc., Chicago, IL, USA) and SAS 9.0 (SAS Institute Inc., Cary, NC, USA).

To avoid potential confounding factors, additional sensitivity analyses will be conducted following these statistical analyses by using STATA (StataCorp, College Station, TX, USA) or R methods. Patient expectations also will be included as ordinal fixed factors in the sensitivity analyses. Full analysis set and the potential confounding factors relating to baseline differences will be used to calculate the results.

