#### Sequence generation

Patients will be randomly allocated to one of two groups in a 1:1 ratio using a minimization procedure controlled by the GCP center. Minimization is used to balance the severity of obesity, age, and gender between the two groups. The severity of obesity is divided into 4 levels, including overweight (24 ≤ BMI < 28), obesity I (28 ≤ BMI ≤ 32), obesity II (32 < BMI < 35), and obesity III (BMI ≥ 35) [26–29]. Once the severity of obesity, age, and gender of the patients are inputted in the online software, the minimization procedure will be implemented by a skilled statistician.

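### Age and gender drive the minimisation but are not named in the primary ANCOVA, and the remaining sensitivity covariates are tied to observed baseline differences

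*Protocol article*

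**What the plan says.** **Allocation** (Protocol article, Sequence generation). Assignment is 1:1 by minimisation: "Minimization is used to balance the severity of obesity, age, and gender between the two groups". Severity has four levels, all defined by BMI cut-points at 28, 32 and 35. The Discussion gives the reason for minimising: it treats obesity level, gender and age as possible confounders.

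**Primary analysis** (Protocol article, Analysis). "The primary outcome is the change of BMI during the 12th week after minimization". For the comparison at 12 weeks, "analysis of covariance (ANCOVA) will be used to adjust for baseline values". The same method is applied to body weight, waist-to-hip ratio, SF-36 and IWQOL-Lite. Neither age nor gender is named in this or any other model.

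**Sensitivity analyses** (same section, last paragraph). One covariate is fixed in advance: "Patient expectations also will be included as ordinal fixed factors in the sensitivity analyses". The others are described only by a rule: "Full analysis set and the potential confounding factors relating to baseline differences will be used to calculate the results".

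**The concern.** Minimisation makes the groups more alike on age and gender than simple randomisation would. A model that leaves these factors out still counts their effect on the outcome as random error. Its standard error therefore describes a design with more chance imbalance than this one has. If age or gender predicts BMI change, the confidence interval is too wide, the test rejects less often than its nominal 5 %, and power is lost.

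The sensitivity rule does not repair this. Read naturally, it brings in covariates according to the differences seen at baseline. That choice depends on the data and on the analyst. It also tends to pass over age and gender, because minimisation has already made them similar between groups.

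**Working it through.** The plan gives no figure for the effect of covariates, so there is none to reproduce on this point. The check asks how a baseline-only ANCOVA behaves under minimisation.

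**Inputs from the protocol article**
- 1:1 minimisation on four BMI bands, age and gender (Sequence generation).
- Significance level 5 %, two-sided because the alternative is stated as ≠; 64 patients per group before dropout, so N = 128 (Sample size calculation; hypotheses in Study design and Analysis).

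**Assumptions not in the article**
- R², the share of the variance left after baseline BMI that age and gender explain. It is varied because no value is given.
- For the simulation: three age bands, 30 % men, and a minimisation probability of 0.8 or 1.0.
- Standardised effect 0.5. At this effect 64 per group has 80 % power (two-sided t-test, 0.801). The article's own inputs, 4.84/7.38 = 0.656, give 37 per group by its formula. That mismatch is a separate matter and nothing here rests on it.

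**Step 1: standard error.** Under near-perfect balance, the baseline-only standard error is too large by the factor 1/√(1 − R²).
- R² = 0.05: 1/√0.95 = 1.03
- R² = 0.10: 1/√0.90 = 1.05
- R² = 0.20: 1/√0.80 = 1.12

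**Step 2: limit for the type I error.** With perfect balance the baseline-only test rejects a true null at the rate 2·[1 − Φ(1.96/√(1 − R²))].
- R² = 0.05: 2·[1 − Φ(2.011)] = 4.4 %
- R² = 0.10: 2·[1 − Φ(2.066)] = 3.9 %
- R² = 0.20: 2·[1 − Φ(2.191)] = 2.8 %

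These are floors, because imperfect balance moves the rate back towards 5 %.

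**Step 3: simulation of minimisation.** N = 128, with 4,000 runs under the null and 2,000 runs at effect 0.5. Ranges cover the two minimisation probabilities.

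| R² | Type I error, baseline BMI only | Type I error, plus age and gender | Power, baseline BMI only | Power, plus age and gender |
|---|---|---|---|---|
| 0 | 0.044-0.054 | 0.045-0.052 | 0.80-0.81 | 0.80 |
| 0.10 | 0.039-0.041 | 0.049-0.052 | 0.82 | 0.85 |
| 0.20 | 0.030-0.033 | 0.050-0.053 | 0.82-0.83 | 0.87-0.88 |
| 0.30 | 0.022-0.025 | 0.050-0.055 | 0.83-0.84 | 0.91-0.92 |

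The Monte Carlo standard error is about 0.3 percentage points for the type I errors (√(0.039·0.961/4000) = 0.003) and 0.9 points for power (√(0.82·0.18/2000) = 0.009).

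**Step 4: cross-check of power.** The non-centrality at effect 0.5 is 0.5·√32 = 2.83. With perfect balance, baseline-only power is Φ((2.83 − 1.96)/√(1 − R²)) and adjusted power is Φ(2.83/√(1 − R²) − 1.96).
- R² = 0.05: 0.81 against 0.83
- R² = 0.10: 0.82 against 0.85
- R² = 0.20: 0.83 against 0.89

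The simulation agrees with the last two pairs to within about a point.

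**The case against.** **The primary covariate list may not be closed.** The text speaks of baseline values in the plural and does not exclude age and gender. The article is condensed, and a full protocol or SAP might list the covariates. This stands in part: that baseline BMI is the only covariate is an inference. But the article does state a model and a rule for further covariates, and neither names two of the three factors used for allocation. If age and gender were meant, the same change of wording settles it.

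**The sensitivity wording can be read otherwise.** The Discussion lists obesity level, gender and age as possible confounders, so the phrase on confounding factors might be meant to include them. This is possible. But the phrase links those factors to baseline differences, and selection by observed imbalance is the more natural reading.

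**The effect may be small.** Nothing in the article says how well age and gender predict 12-week BMI change once baseline BMI is in the model. This stands, which is why the size is given as a range. Power also suffers less if the true effect is larger. At the article's 0.656, the Step 4 formulas (non-centrality 0.656·√32 = 3.71) give 0.967 against 0.974 at R² = 0.10, less than one point.

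**Stronger readings that the article does not support.** A reader might infer any of the following.
- *All three minimisation factors are ignored.* Severity is a banding of BMI, and baseline BMI carries it.
- *The trial risks false positives or a biased estimate.* The error runs the other way: the test is conservative and the estimate is unbiased.
- *The primary result depends on covariates chosen after the fact.* The baseline-difference rule appears only in the paragraph on sensitivity analyses.
- *No sensitivity covariate is prespecified.* Patient expectations are.

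**Conclusion.** The point holds as a mismatch between the allocation and the analysis as stated, limited to age and gender. Its harm is a standard error that is too large and some lost power, and it grows with R². At 5 % or less it can be ignored; at 10 % it costs about 3 power points at effect 0.5, and at 20 % about 5. The direction follows from the design. The size rests on the assumed R² and, less strongly, on the assumed minimisation settings and effect size.

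The baseline-difference rule is a second, smaller defect. It weakens the supporting analyses without touching the primary test.

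**What to change.** State the primary ANCOVA as group + baseline BMI (continuous) + age (continuous) + gender. In the sensitivity analyses, replace the rule based on baseline differences with a list fixed in advance: these covariates plus the expectation score that is already planned.

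The study assistant already sends gender, date of birth and BMI to the GCP center for allocation (Implementation), so no new data are needed. The cost is wording and two degrees of freedom. If age and gender turn out not to be prognostic, no more than about one power point is lost (in the simulation at R² = 0, 0.8085 against 0.803 and 0.8035 against 0.7995). The article reports that recruitment is under way and that the statistician stays blinded until the end of the study, so the model can still be fixed before unblinding.

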**Methods/Design:**

To compare the effectiveness of acupuncture plus lifestyle modification, a 2-armed, controlled trial with randomization using minimization will be conducted on 150 simple obesity and overweight patients, aged 18–50 years, for a 36-week study duration. All patients will be randomly assigned to one of two groups and will receive either acupuncture plus lifestyle modification or lifestyle modification alone. Outcomes will be evaluated at baseline and at 4 weeks, 8 weeks, and 12 weeks during treatment as well as at 6-week, 12-week, and 24-week follow-up. The primary endpoint is change of body mass index (BMI) during the 12th week. Secondary endpoints are body weight; waist-to-hip ratio; biochemical tests including serum cholesterol (TC), triglyceride (TG) and high-density lipoprotein (HDL) levels; and answers to the Short Form 36 (SF-36) and the Impact of Weight on Quality of Life Questionnaire-Lite Version (IWQOL-Lite). Statistical analyses will be based on the intention-to-treat (ITT) principle. The main endpoint will be analyzed by analysis of covariance (ANCOVA), and the objective outcome results will be analyzed by logistic regression analysis. To avoid potential confounding factors, additional sensitivity analyses will be conducted following these statistical analyses.

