## Methods

### Study design

A randomized, controlled, 2-armed trial using a parallel design with a 36-week study duration for each patient will be conducted to test 2 different hypotheses:

H_0_: acupuncture plus lifestyle modification = lifestyle modification (null hypothesis) versus H_1_: acupuncture plus lifestyle modification ≠ lifestyle modification (alternative hypothesis).

To test these hypotheses, patients will be randomized into one of two groups as shown in Fig. 1.

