#### Outcomes

The primary outcome is the change of BMI during the 12th week after minimization. The formula for BMI is as follows:

BMI = mass (kg)/(height(m))^2^.

The BMI of all patients will be calculated at baseline; during treatment at 4, 8, and 12 weeks; and 6-week, 12-week, and 24-week follow-up [39]. The BMI reduction will be assessed by a blinded investigator from the Clinic of Nanjing University of Chinese Medicine.

The secondary outcomes are divided into objective outcomes and patient-centered outcomes. The body weight and the waist-to-hip ratio will be used as supplementary measures in combination with the BMI, and will be calculated at baseline; during treatment at 4, 8, and 12 weeks; and at 6-week, 12-week, and 24-week follow-up. In addition, TC, TG, and HDL levels also will be tested at baseline; during treatment at 4, 8, and 12 weeks to assess the metabolic changes [40]. For patient-centered outcomes, IWQOL-Lite and SF-36 are used to measure obesity-specific quality of life. The IWQOL-Lite questionnaire is a validated, obesity-specific measure, consisting of 31 items regarding the impact of obesity on physical function, self-esteem, sexual life, public distress, and work [41–43]. Patients will be asked to rank items related to obesity in 5 areas, ranging from 5 “always true” to 1 “never true”, by an independent assessor. The independent assessor will give a detailed explanation regarding every item of this questionnaire to patients before the treatment. All the patient-centered outcomes will be detected before treatment; during treatment at 4, 8, and 12 weeks; and at 6-week, 12-week, 24-week follow-up. Adverse events and serious adverse events will be recorded during the study to assess safety. By using a valid expectation questionnaire relating to acupuncture [44], participants’ expectations for acupuncture at baseline will also be assessed.

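### Bonferroni is prescribed for two primary analyses, but the protocol identifies only one, so the threshold for the primary test can be read as 0.05 or 0.025

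*Protocol article*

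**What the plan says.** All references are to the protocol article.

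- **Analysis, on multiplicity:** "Because there are two primary analyses (electro-acupuncture plus lifestyle modification versus lifestyle modification alone), Bonferroni correction will be used to address multiple testing". The sentence closes with "a significance level of 0.05 will be used" and does not say whether that level is per test or family-wise.
- **Analysis, on the primary method:** "To determine differences between the 2 groups after 12 weeks, analysis of covariance (ANCOVA) will be used to adjust for baseline values".
- **Outcomes:** "The primary outcome is the change of BMI during the 12th week after minimization". Body weight appears there among the secondary outcomes.
- **Abstract, Methods/Design:** "The primary endpoint is change of body mass index (BMI) during the 12th week. Secondary endpoints are body weight".
- **Study design:** "A randomized, controlled, 2-armed trial using a parallel design with a 36-week study duration" which "will be conducted to test 2 different hypotheses". What follows is one null hypothesis and its two-sided alternative. The Analysis section repeats the same pair.
- **Sample size calculation:** 80 % power at a 5 % significance level, 64 per group, 150 in total. No multiplicity adjustment is mentioned.
- **Aims:** the main objective is to be assessed by both BMI and body weight.

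**The concern.** A Bonferroni correction needs a family of at least two tests. The sentence that prescribes it asserts two primary analyses and then describes one treatment contrast. In a two-arm trial with one primary endpoint at one time point there is only one primary test, and the article nowhere says what the second would be.

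This matters because the sentence fixes the rule for declaring the trial positive. An analyst who takes the word two at face value tests BMI at 0.025. An analyst who counts the tests actually defined uses 0.05. Both can cite the protocol. If the primary p-value falls between the two levels, the conclusion depends on a choice that could be made after the result is known. If 0.025 is used for a single test, power is given up with nothing gained in control of false positives that the plan needs.

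**Working it through.** **Step 1. Count the primary tests.**

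| Element | Number | Where stated |
|---|---|---|
| Between-group comparisons | 1 (two arms) | Study design |
| Primary endpoints | 1 (BMI change) | Abstract, Outcomes, Analysis |
| Primary time points | 1 (week 12) | Abstract, Outcomes, Analysis |
| Null/alternative pairs | 1 | Study design, Analysis |

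Number of primary tests m = 1 × 1 × 1 = 1. The two hypotheses announced under Study design are the null and the alternative of this one test.

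**Step 2. Derive the threshold.** The Bonferroni per-test level is 0.05/m.

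- m = 1: 0.05/1 = 0.05. The correction changes nothing.
- m = 2, as the sentence asserts: 0.05/2 = 0.025.

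**Step 3. Ask whether the sample size reveals which level was meant.** The article's formula with k = 1 is n = (u_α + u_β)² × 2 × σ²/δ², with δ = 4.84 kg and σ = 7.38 kg.

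- 2 × 7.38²/4.84² = 2 × 54.464/23.426 = 4.650.
- Two-sided 0.05, 80 % power: (1.960 + 0.842)² × 4.650 = 36.5, so 37 per group.
- Two-sided 0.025, 80 % power: (2.241 + 0.842)² × 4.650 = 44.2, so 45 per group.

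Neither gives the stated 64. That discrepancy is a separate matter. Here it means only that the sample size does not show a corrected level to have been in use. The dropout step is close to the stated total: 64/0.85 = 75.3 per group, against 150 in total (75 per group).

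**Step 4. Power at the two thresholds with the planned 64 per group.** Two-sample t test, two-sided, 126 degrees of freedom, noncentrality d × √(64/2). Critical values are 1.979 at 0.05 and 2.269 at 0.025.

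| Standardised difference d | Source | Noncentrality | Power at 0.05 | Power at 0.025 | Loss (points) |
|---|---|---|---|---|---|
| 4.84/7.38 = 0.656 | Sample size calculation (body weight) | 3.710 | 95.7 % | 92.4 % | 3.3 |
| 0.50 | Assumption, not in the article | 2.828 | 80.1 % | 71.2 % | 8.9 |

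The second row is shown because d = 0.50 gives the stated 80 % power at 64 per group. The article gives no expected difference or standard deviation for BMI, so the power for the actual primary endpoint cannot be computed from it.

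**The case against.** **The two levels need not contradict each other.** A reader might infer that the sentence sets two incompatible significance levels. It does not have to: 0.05 can be the family-wise level and 0.025 the per-test level, which is ordinary Bonferroni usage. This objection stands. The defect is that the second analysis is unidentified and the per-test level unstated. On this reading the unadjusted 5 % in the sample size section remains unexplained.

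**A second primary analysis may have been intended.** The Aims name BMI and body weight together, and the trial is sized on body weight. So it cannot be said with certainty that there was never anything to correct. However, the Abstract and the Outcomes section make body weight secondary, and the parenthesis in the Bonferroni sentence describes a treatment contrast, not a pair of endpoints. One primary test is the better supported reading, but the fix should leave room for the other.

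**Nothing becomes anti-conservative.** This is correct. A single test at 0.05 is valid and at 0.025 is conservative. If two were truly intended, 0.025 each controls the family-wise rate. A reader might infer an inflated false-positive risk from the muddled sentence, but neither reading of it produces one.

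**The power loss may be small.** Also correct on the article's own inputs, where it is about 3 points and power stays above 90 %. A fall from 80 % to 71 % should not be presented as this trial's power, because it depends on an assumed standardised difference.

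**A statistical analysis plan could settle it.** A later plan could clarify the level, but this is not a detail left open for it. The protocol states a premise that the rest of its text does not bear out and attaches a correction to it.

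**Conclusion.** The point holds. The protocol prescribes a multiplicity correction without identifying a second primary test, and so leaves the success threshold for the primary analysis at either 0.05 or 0.025. This rests on the wording alone and needs no assumption about effect size.

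The practical consequence is confined to a primary p-value between 0.025 and 0.05, together with the power lost if the stricter level is applied to one test. That loss is 3.3 percentage points under the stated body-weight inputs and 8.9 under an assumed standardised difference of 0.50, both at 64 per group. Neither figure is the power for BMI, which the article does not allow one to calculate. The primary endpoint, time point, contrast and method are otherwise named consistently. The correction is still needed, because the affected sentence decides whether the trial is declared positive.

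**What to change.** Make the change by a dated amendment before unblinding. The Trial status section says that recruitment is under way, and dropping a correction can be seen as relaxing the threshold from 0.025 to 0.05. The Blinding section keeps the statistician blind to group identity until the end of the study, so an amendment made now can be shown to be independent of the results.

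1. **Analysis:** delete the Bonferroni sentence. State that there is one primary analysis, the between-group difference in BMI change from baseline to week 12, tested two-sided at 0.05 with no multiplicity adjustment.
2. **Study design:** replace the reference to two different hypotheses with wording that introduces the single hypothesis that follows.
3. **Alternative, if a second primary analysis was intended** (for example body weight, as the Aims might suggest): name it as primary throughout, state 0.025 per test, and restate the sample size or the power at that level.

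The first route costs two sentences of wording and the amendment itself, with no change to trial conduct. The second also requires the sample size or power to be recalculated, and the Abstract and Outcomes sections to be brought into line.

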### Patients

To be included in this study, patients need to fulfill the following criteria: be male or female, aged 18–50 years old, and have a BMI ≥ 24 kg/m^2^, as diagnosed by their general physician in accordance with the guidelines of prevention and treatment for overweight and obesity in Chinese adults [24]. The patients should have failed previously to achieve their weight-loss goals through diet and exercise alone, and be willing to accept acupuncture and lifestyle modification after the explanation of risks and benefits regarding these two therapies. In addition, the ability to read and understand consent forms and questionnaires is required.

Patients will be excluded if they meet the following criteria: they have inherited obesity or secondary obesity; an endocrine disease such as a thyroid disorder, pituitary disorder, or sex gland disorder; heart disease such as arrhythmia, heart failure, myocardial infarction, or require a pacemaker; allergic or immune disease; kidney disease such as diabetic nephropathy, secondary focal segmental glomerulosclerosis, high amino transferases (alanine, aspartate > 50 U/L), or high serum creatinine (4.25 mg/dL); or are a pregnant or lactating woman. In addition, patients who have managed their weight for 1 month or have any other conditions unsuitable for this trial as evaluated by a general physician will be excluded.

All patients will be recruited in outpatient clinics of the Affiliated Hospital of Nanjing University of Chinese Medicine. Additional advertisements will be conducted in five universities in Nanjing, China. *The Handbook of Obesity* will also be printed and sent to all patients.

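### LOCF is the only stated missing-data method for a changing weight outcome, so dropout biases the week-12 difference in a direction that cannot be known in advance

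*Protocol article*

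**What the plan says.** The endpoint and model are in the protocol article, Analysis: "The primary outcome is the change of BMI during the 12th week after minimization", for which "analysis of covariance (ANCOVA) will be used to adjust for baseline values". The same section extends the model: "ANCOVA will be subsequently performed on BMI, body weight, and waist-to-hip ratio data as well as SF-36 and IWQOL-Lite". The missing-data rule follows directly: "Missing values will be addressed using the methods of last observation carried forward (LOCF"). It is not limited by outcome or visit.

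The analysis is by intention to treat. Everyone with baseline data is to be "included in the analyses, regardless of whether or not they complete the treatment or adhere to the protocol". Dropouts therefore enter through carried-forward values, and a patient seen only at baseline is scored as zero change.

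Under Outcomes, BMI is measured at baseline and then "during treatment at 4, 8, and 12 weeks; and 6-week, 12-week, and 24-week follow-up". Body weight, waist-to-hip ratio and the questionnaires follow the same schedule.

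The sensitivity analyses in the Analysis section are aimed at confounding. They add patient expectations as a factor, and "Full analysis set and the potential confounding factors relating to baseline differences will be used to calculate the results". Sample size calculation allows for 15 % dropout in each group.

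**The concern.** LOCF is exact only if a patient's value stays where it was at the last visit. In a weight-loss trial that is unlikely in either phase. If weight is still falling during treatment, LOCF understates the week-12 loss of early dropouts. If weight returns after treatment, LOCF overstates what is maintained by patients lost during follow-up. The filled values are also analysed as if they had been observed.

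The two arms need not be affected equally. Under Patients, "The patients should have failed previously to achieve their weight-loss goals through diet and exercise alone", and they must be willing to accept acupuncture. Half are then given lifestyle modification alone, without blinding, which could raise control dropout. The other arm is asked to attend 36 acupuncture sessions, three a week, which could raise dropout there. The primary contrast would then partly reflect who left and when. Adding covariates to LOCF-filled data does not correct the filled values.

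**Working it through.** **Inputs from the protocol article.** The planning effect is 4.84 kg with SD 7.38 kg, and dropout is 15 % per group (Sample size calculation). A pooled effect of 1.72 kg against lifestyle modification is cited in Background. On-treatment visits are at weeks 4, 8 and 12. With 150 enrolled there are 75 per arm, and 75 × 0.85 = 63.75, which agrees with the stated 64 per group after dropout. The plan gives no figure for the effect of LOCF, so there is none to reproduce.

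**Assumptions not in the documents.** Controls lose 3 kg by week 12, and loss is linear in both arms. Dropouts' last visit is equally often baseline, week 4 or week 8. Had they stayed, they would have followed their arm's course.

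**Formula.** A dropout keeps on average (0 + 1/3 + 2/3)/3 = 1/3 of the week-12 change and so misses 2/3 of it. With true difference D and dropout shares dA (acupuncture) and dC (control):

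LOCF difference = (3 + D)(1 − 2dA/3) − 3(1 − 2dC/3)

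**Week 12, D = 4.84 kg**

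| Dropout, acupuncture / control | Calculation | LOCF difference | Shift |
|---|---|---|---|
| 15 % / 15 % | 7.84 × 0.900 − 3 × 0.900 | 4.36 kg | −10 % |
| 10 % / 20 % | 7.84 × 0.933 − 3 × 0.867 | 4.72 kg | −3 % |
| 20 % / 10 % | 7.84 × 0.867 − 3 × 0.933 | 4.0 kg | −17 % |
| 5 % / 25 % | 7.84 × 0.967 − 3 × 0.833 | 5.1 kg | +5 % |

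The effect is inflated only when 3dC exceeds 7.84dA, that is, when control dropout is more than about 2.6 times acupuncture dropout.

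**Week 12, D = 1.72 kg.** Equal 15 % gives 1.72 × 0.90 = 1.55 kg. A 5 % / 25 % split gives 4.72 × 0.967 − 3 × 0.833 = 2.06 kg, and the reverse gives 4.72 × 0.833 − 3 × 0.967 = 1.03 kg. Inflation here needs a dropout ratio of only about 1.6 (4.72/3).

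**No true effect.** The false difference is 3 × (2/3) × (dC − dA).
- 15 % / 15 %: zero.
- 10 % / 20 %: 2 × 0.10 = 0.2 kg.
- 5 % / 25 %: 2 × 0.20 = 0.4 kg.

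At SD 7.38 kg the standard error is 7.38 × √(2/75) = 1.21 kg. Two-sided type I error by normal approximation is 5.3 % for 0.2 kg and 6.3 % for 0.4 kg. Simulated trials with these inputs agree, giving about 5 to 7 %. At an assumed SD of 3 kg the standard error is 0.49 kg, and the 0.4 kg artefact gives about 13 %.

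**Follow-up.** Further assume D = 4.84 kg at week 12, regain of a share r (30 to 50 %) of the week-12 loss by the last visit, and dropout only after week 12. Each arm's LOCF mean is its week-12 loss × [(1 − d)(1 − r) + d]. With 15 % lost in both arms the difference is overstated by a factor 0.745/0.70 to 0.575/0.50, that is 6 to 15 %. With 20 % / 10 % it is overstated by 11 to 26 %, and with 10 % / 20 % by 2 to 4 %.

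**Scale.** The planning figures are in kilograms, while the primary outcome is BMI. At assumed heights of 1.60 to 1.70 m, 0.4 kg is about 0.16 to 0.14 kg/m².

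**The case against.** The strongest defence is that on the protocol's own numbers the harm is small and often conservative. With SD 7.38 kg, 15 % dropout in each arm and no true effect, LOCF is unbiased and the test keeps its 5 % level. With a true effect of the planned size, LOCF usually shrinks it. This stands, and it limits the size of the point. It does not make the estimate right: a 10 % understatement under the planned dropout is still a bias.

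Three stronger readings are tempting, and the documents do not support them.
- **LOCF favours acupuncture.** Nothing shows which arm will lose more patients. Controls receive an individual plan, 12 consultations and a social network meant to sustain participation, while the acupuncture arm carries a heavy visit schedule. Even with twice the dropout among controls (10 % / 20 %), a true 4.84 kg is understated.
- **Type I error is badly inflated.** The 13 % figure needs both a 5 % / 25 % split and an SD of 3 kg. Neither is in the documents.
- **End-of-treatment weight is carried through follow-up for all dropouts.** That holds only for patients lost after week 12. Earlier dropouts carry an earlier value, and the primary contrast at week 12 is untouched by this.

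It is also fair that an article may leave missing-data sensitivity analyses to an analysis plan that is not shown. Their absence is therefore not the finding. The finding is that LOCF is the stated main method.

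**Conclusion.** The point holds as a should-fix on the choice of method. LOCF is fixed as the sole method for BMI, body weight, waist-to-hip ratio and the questionnaires at every visit, and it suits an outcome that is expected to move poorly. Its effect on the week-12 difference cannot be signed beforehand. In the scenarios worked for a true 4.84 kg, it ranges from about −17 % to +5 %, with −10 % under equal 15 % dropout. With no true effect and more control dropout, the artefact is 0.2 to 0.4 kg and type I error stays at about 5 to 7 % at the stated SD. At the secondary follow-up visits, LOCF assumes no regain after the last observation and can overstate maintenance in patients lost after week 12.

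That LOCF is the stated method is certain. The sizes are illustrative. They rest on the assumed 3 kg control loss, linear course, timing of dropout and regain, and on dropouts otherwise behaving like the rest of their arm.

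**What to change.** Replace LOCF in the main analysis of BMI, body weight, waist-to-hip ratio, SF-36 and IWQOL-Lite. Use a likelihood-based mixed model for repeated measures with baseline value, group, visit and group-by-visit terms, fitted to the visits already scheduled, with the week-12 BMI contrast as primary. ANCOVA after multiple imputation that uses the intermediate visits is an acceptable alternative.

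Keep LOCF as a sensitivity analysis only. Both replacements assume missing at random, which disappointed or overburdened patients may violate. So add a sensitivity analysis that departs from that assumption separately by arm, such as delta-adjusted or reference-based imputation.

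The cost is slightly more analysis work, in SAS, Stata or R, all already named, and reliance on a missing-at-random assumption in the main analysis. No extra patients, visits or data are needed. The article reports that recruitment is under way, so the change should be documented before the statistician is unblinded.
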